**Fig. 1 Fig1:**
[figure not shown]
Study design and key assessments. Study design and data collection overview. PI = pulsatility index; PP = postpartum; * Assessments at moment of diagnosis; ** Laboratory parameters tested include NLR, MPV (mean platelet volume), platelet count, Fe, transferrin and ferritin

FMD and PAT measurements will be performed simultaneously and patients will be asked 24 h prior to examination not to eat high-fat substances nor drink caffeine or alcohol and to refrain from smoking at least 6 h prior to examination. Fingernails had to be short and no nail polish applied. Patients were studied in a quiet, temperature-controlled room (21-24 °C) and stressful situations for the patient were avoided (people entering the room unexpectedly, telephone ringtones, etc.) Patients will not by measured in active labour.

##### Endothelial function (RHI)

PAT is recorded using the Endo-PAT2000® (Itamar Medical, software version 3.2.4) and the disposable fingertip probes (Itamar Medical) in accordance with the manufacturer’s recommendations. PAT is a less operator-dependent and more reproducible technique. The system uses pneumatic finger probes which assess digital volume changes accompanying pulse waves. Reactive hyperaemia is induced as described for FMD and measurements are performed simultaneously to FMD. The ratio of the average amplitude of the PAT signal over a 1 min period starting 1 min after cuff deflation (maximum pulse amplitude) divided by the average amplitude of the PAT signal over a 3.5 min period before cuff inflation (baseline pulse amplitude) is calculated. The control arm is used to correct for confounding factors (room temperature, systemic changes). The result is expressed as the reactive hyperaemia index (RHI) (Fig. 2). All recordings are performed simultaneously with the FMD and by the same two experienced investigators ([name]).

**Fig. 2 Fig2:**
[figure not shown]
Representative reactive hyperaemia peripheral arterial tonometry recordings of subjects with normal and abnormal reactive hyperaemic response. Normal response is characterized by a distinct increase in the signal amplitude after cuff release compared with baseline

##### Arterial stiffness: PWV, AP, AIx and AIx75

Pulse wave velocity and pulse wave analysis will be calculated using the Sphygmocor system ® (Atcor Medical, West Ryde, Australia). To calculate PWV, two pressure waveforms must be measured at a known distance apart and the distance between measurement sites is divided by the propagation time. Aortic PWV is measured by carotid-femoral PWV (cfPWV) as it is the ‘gold standard’ measurement of the stiffness of the aorta. Measurements of cfPWV will be performed using a pressure tonometer to transcutaneously record the pressure pulse waveform in the underlying artery. The tonometer contains a micromanometer that provides a very accurate recording of the pressure within the artery. The carotid and femoral PWV will be assessed by gently compressing respectively the carotid artery and the femoral artery with the tip of the tonometer at the site of maximal pulsation. The Sphygmocor device will automatically calculate the cfPWV.

Pulse wave analysis will calculate AIx by placing the tonometer at the radial artery (site of maximum pulsation). A generalized transfer function will derive the aortic pressure waveform from the radial artery waveform. From the aortic pressure waveform, the augmentation pressure (AP) and augmentation index (AIx) can be calculated. The AP (ΔP) is defined as the height of the late systolic peak above the inflection point on the waveform. The AIx is defined as AP expressed as a percentage of the aortic PP. As AIx is affected by heartrate, it will be standardized to a heart rate of 75 bmp (AIx-75).

##### Pulsatility index uterine artery and fetal biometry

Uterine artery Doppler examinations will be performed using trans-abdominal colour directed pulsed wave Doppler (Voluson, GE Healthcare Technologies, USA). Pulsatility index of both uterine arteries will be obtained on either side of the cervix before 14 weeks’ gestation and at the apparent crossover with the external iliac arteries after 14 weeks [28, 29].

Three similar consecutive waveforms must be obtained before calculating the PI. The mean PI of the two vessels was calculated. Observation on the presence or absence of a bilateral early protodiastolic notch will be performed. A notch is defined as a persistent decrease in blood flow velocity below the diastolic peak velocity, in early diastole.

At the same moment basic fetal biometry parameters will be measured: bi-parietal diameter, head circumference, abdominal circumference, femur length and expected fetal weight using Hadlocks formula [30].

##### Markers of systemic inflammation

Performing a complete blood count (CBC), the neutrophil/lymphocyte ratio (NLR), mean platelet volume (MPV) and platelet count will be obtained using a ADVIA 120 Hematology System (Siemens healthcare, Germany) [31–33].

##### Automated blood pressure measurement

SBP, DBP and MAP after 10 min rest in a sitting position, will be measured using a Mindray VS 900 monitor (Mindray ®, China).

#### Oxidative stress

##### Electron paramagnetic resonance

EPR (electron paramagnetic resonance) is derived from magnetic resonance spectroscopy and uses microwave radiation to detect molecules with an unpaired electron number, like radicals. When an magnetic field is created by the EPR spectrometer, all radicals will align. The EPR spectrometer sends out a radio frequent microwave, causing the electrons to jump from a low to a high energy state. This energy absorption can be measured and is directly correlated to the amount of free radicals in the sample. A ‘spin trap’ will be added to scavenge the very reactive radicals and to prolong their half live. EPR spectra will be obtained using the Bruker EMX 1273 spectrometer equipped with an ER 4119HS high-sensitivity resonator (=cavity) and 12-kW power supply operating at X band frequencies. The Bruker WINEPR -post processing system software (Germany, 1996) will be used to analyse the spectra [34].

##### Placental concentration of •NO

Placental tissue will be obtained within 2 min after (vaginal or caesarean) delivery. At a standardized central location, a viable sample of 1cm^3^ placental tissue will be taken avoiding placental infarcts. The sample will be rinsed with saline (NaCl) and immediately added to the spin trap 750 μl FeSO4 + 750 μl DETC (iron (II) diethyldithiocarbamate solution). After 1 h of incubation at 37 °C, the sample will be snap frozen and stored in − 80 °C until analysis with EPR [34].

Since labour causes ischemia-reperfusion injury at the site of the placenta, which will influence placental NO concentrations, samples will be subdivided in labour (vaginal delivery, secondary caesarean section) versus no labour (elective caesarean section) [35].

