In normal pregnancy, placental OS is present during all three trimesters and is necessary to obtain normal cell function, including activation of redox-sensitive transcription factors and activation of protein kinases [11–15]. Although OS is a common necessary feature of normal pregnancy, persistent OS gives rise to different disease-states, such as PE [13, 15–17]. Although considerable research has been devoted to OS in PE [13–15], less attention has been paid to the evolution of OS during the course of normal pregnancy. Little research has described an increase in •NO concentration with gestational age, suggesting an important role for •NO in the cardiovascular changes of normal pregnancy [3].

Recent literature has elucidated that PE is an important risk factor for cardiovascular disease in later life. Bellamy et al. and McDonald et al. describe a 3-fold risk for hypertension and a 2-fold risk of ischemic heart disease and stroke in women with a history of PE [18–21]. Women with hypertensive disorders during pregnancy also have a greater risk of chronic kidney disease and end-stage renal disease [22, 23]. With a view to detecting those women at risk, objectifying endothelial function and vascular function after healthy pregnancy and PE can help to establish reference values for disturbed post-pregnancy vascular function.

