### Objectives

#### Primary study objective

To evaluate OS during pregnancy.

Measurement of •NO in placental tissue and O_2_•^−^ in maternal blood using EPR.

Measurement of eNOS in placental tissue using immuno-histochemical staining.

*Prospective longitudinal study*: To evaluate the OS profile in normal pregnancies.

*Matched case-control study:* To compare the OS profile in normal versus PE pregnancies.

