##### Multicentre matched case-control study

The second part is a case control study where patients with pregnancies complicated by PE will be compared to normotensive controls, matched for maternal and gestational age, parity, smoking behaviour, BMI and ethnic group. Patients will be followed throughout (the rest of their) pregnancy and until 6 months postpartum. Matching will reduce the risk of bias.

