##### Matched case-control study

RHI, FMD, PWV/PWA, UA Doppler PI, fetal biometry, NLR, MPV, MAP, birth-weight, eNOS, •NO and O_2_•^−^ concentration and other continuous variables in PE versus healthy pregnancies will be tested for normality using the Shapiro Wilk Test. If there is normality, they will be expressed as mean, standard deviations and 95% confidence intervals and compared using two sided T test. If not, they will be expressed as median and interquartile ranges and compared using Mann Whitney U Test.

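### The case-control test for placental •NO and eNOS makes no use of the labour subdivision or of gestational age at delivery, although the article links •NO to both labour and gestational age

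*Protocol article*

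**What the plan says.** All references are to the protocol article.

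- **Primary study objective.** It includes "Measurement of •NO in placental tissue and O_2_•^−^ in maternal blood using EPR" and "Measurement of eNOS in placental tissue using immuno-histochemical staining". The case-control aim is "To compare the OS profile in normal versus PE pregnancies". The Study hypothesis expects lower placental •NO and eNOS in pre-eclampsia (PE).
- **Study design, Multicentre matched case-control study.** Controls are "matched for maternal and gestational age, parity, smoking behaviour, BMI and ethnic group". No time point is given for the gestational-age match, and labour and mode of delivery are not matching factors. "Patients will be followed throughout (the rest of their) pregnancy and until 6 months postpartum". The Inclusion criteria admit women beyond 20 weeks, and the Fig. 1 legend marks some assessments as made at diagnosis.
- **Placental concentration of •NO.** Tissue is taken within 2 minutes of delivery. The section states that labour will affect placental •NO, and so "samples will be subdivided in labour (vaginal delivery, secondary caesarean section) versus no labour (elective caesarean section".
- **Immuno-histochemical staining for eNOS and iNOS.** Tissue again comes from delivery. No labour split is mentioned.
- **Background.** It cites limited research reporting an increase in •NO "concentration with gestational age, suggesting an important role for" •NO in the cardiovascular changes of normal pregnancy.
- **Statistical methods, Matched case-control study.** One list covers the vascular measures together with "fetal biometry, NLR, MPV, MAP, birth-weight, eNOS", •NO, superoxide and other continuous variables. After a normality test, all of them go to a two-sided t test or a Mann-Whitney U test. No stratum, covariate or pairing is named.

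**The concern.** The article gives a reason to separate placental samples by labour, but the analysis section names a test for the same variable that does not use the separation. This is a stated test that leaves out an influence the article itself names, so it is more than detail left to a fuller document. eNOS comes from the same placentas and has no labour step at all.

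Gestational age raises a second difficulty. A match made at inclusion balances gestational age on that day. It does not balance it at delivery, when the placenta is sampled. If •NO rises with gestation and cases deliver earlier, the unadjusted comparison would show lower •NO in PE even without a disease effect, which is the hypothesised direction. The direction of any labour bias cannot be told from the document, which does not say whether labour raises or lowers •NO.

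At stake is whether a placental difference, part of the primary objective, could be attributed to PE.

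**Working it through.** **1. The plan's own figure.** The case-control sample size rests on RHI: difference 0.3, SD 0.5, two-sided α 0.05, power 80%.

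n = 2 × (1.96 + 0.8416)² × 0.5² / 0.3² = 43.6, so 44 per group, as stated. At the planned 45 per group, power is 81% (normal approximation) or 80% (t test). The standardised effect is 0.3/0.5 = 0.6 SD. No SD or effect size is given for placental •NO or eNOS, so the steps below work in SD units.

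**2. False-positive rate for a given spurious difference.** With no true PE effect, 45 per group and a spurious difference b in SD units, the test statistic is centred at b / √(2/45). The rejection rates for a two-sided t test at 5% are:

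| b (SD) | false-positive rate |
|---|---|
| 0 | 5% |
| 0.15 | 11% |
| 0.30 | 29% |

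**3. How labour could produce such a difference (all inputs assumed).** b = labour effect × difference in labour shares. The rates here use a normal approximation and allow for the extra variance from mixing labour and no-labour samples.

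| Labour effect (SD) | Labour share, cases / controls | Size of b (SD) | false-positive rate |
|---|---|---|---|
| any | 50% / 50% | 0 | 5% |
| 0.25 | 50% / 80% | 0.075 | 6% |
| 0.5 | 50% / 80% | 0.15 | 11% |
| 1.0 | 50% / 80% | 0.30 | 25% |
| 0.25 | 30% / 80% | 0.125 | 9% |
| 1.0 | 30% / 80% | 0.50 | 59% |

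**4. How gestational age at delivery could do so (all inputs assumed).** b = slope per week × gap in weeks; normal approximation.

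- 0.02 SD per week × 2 weeks = 0.04 SD: 5%
- 0.05 SD per week × 4 weeks = 0.20 SD: 16%
- 0.10 SD per week × 6 weeks = 0.60 SD: 81%

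The spread shows that the document does not determine the size. It is not an estimate of the bias.

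**5. What labour stratification costs.** For a true effect of 0.6 SD (borrowed from RHI), each stratum contributes information w = 1/(1/n₁ + 1/n₂), where n₁ and n₂ are its numbers of cases and controls. The strata are summed, and power = Φ(0.6 × √Σw − 1.96). For shares of 50% and 80%: labour stratum 22.5 v 36, w = 13.85; no-labour stratum 22.5 v 9, w = 6.43; sum 20.27; power = Φ(2.70 − 1.96) = 77%.

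| Labour share, cases / controls | Combined strata | Labour stratum alone | No-labour stratum alone |
|---|---|---|---|
| 50% / 50% | 81% | 52% | 52% |
| 50% / 70% | 80% | 58% | 41% |
| 50% / 80% | 77% | 61% | 33% |
| 30% / 80% | 69% | 47% | 35% |

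Combining the strata keeps most of the power. Reading one stratum on its own does not.

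**The case against.** The best defence is that labour has been considered: the article plans the subdivision, and comparing cases with controls within labour strata is a standard control for confounding. Covariates and sensitivity models are also often left to a fuller analysis plan. Both points have weight. What remains is that the analysis section names a test for •NO without using the split, and that eNOS and iNOS have no split.

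Several stronger readings are tempting, but the document does not support them.

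- **That matching is known to be at assessment.** This is a fair inference from entry after 20 weeks, later follow-up and the Fig. 1 legend. The article never says it.
- **That PE cases deliver earlier or labour less often than controls.** No delivery timing or delivery mode by group is given. Both are assumptions.
- **That placental •NO and eNOS are shown to depend on gestational age.** The Background sentence does not say that the rise was in placental tissue, and it does not mention eNOS.
- **That unplanned caesareans before labour are misclassified.** The article does not define a secondary caesarean. It may mean one performed in labour, in which case an unplanned caesarean before labour simply has no stated class.
- **That subdividing by labour costs so much power that it cannot help.** Power near 50% applies to a single stratum, and the article does not say that only one would be used.

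Adjusting for gestational age at delivery can also be disputed. If PE brings delivery forward, this variable lies partly on the pathway from disease to outcome, and adjustment may remove part of the effect of interest. That objection stands and shapes the fix. The different wording for birth weight in the two analysis sections may be shorthand and has no bearing on this point.

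**Conclusion.** The point holds in a limited form. The stated comparison of placental •NO and eNOS is unadjusted and unpaired. It does not use the labour split that the article itself motivates, and nothing in the article secures balance in gestational age at delivery. Confounding of the primary placental result is therefore a real risk, but not a demonstrated bias.

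Its size rests wholly on assumed inputs. A spurious 0.15 to 0.30 SD gives an 11% to 29% false-positive rate with 45 per group, and there is no inflation if labour shares and delivery ages are alike in the two groups. The labour part rests on the article's own statement about placental •NO. The gestational-age part is weaker, because it needs both the inferred time point of matching and an extension of the Background sentence to placental tissue.

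**What to change.** In the case-control analysis section:

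1. Compare placental •NO, eNOS and iNOS between cases and controls with labour (yes/no) as a stratum or covariate, combining the strata into one estimate.
2. Code labour by whether it had begun, so that every caesarean has a class.
3. Report beside this a prespecified result further adjusted for gestational age at delivery, and note that this variable may lie partly on the PE pathway.

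In the study design section, state the time point at which gestational age is matched.

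The cost is analysis wording and one coding rule, with no new visits or samples. Some power is lost if labour shares differ: about 69% to 81% remains for 0.6 SD in combined strata, against 81% unadjusted. Adjustment for gestational age will be weak for very early deliveries that have no comparable control.

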##### Matched case-control study

In a pilot study by Yinon [38] the RHI in normotensive pregnancies was 1.8, and in PE 1.5; in most populations standard deviation is 0.5 [37]. For 80% power and a two sided α = 0.05 and considering a 0.3 difference clinically relevant, the sample size for each group would be 44 *(**http://www.stat.ubc.ca/~rollin/stats/ssize/n2.html**);* which we consider the sample size for our cross-sectional study comparing pre-eclamptic patients with normotensive controls. The sample size of this study will be 90 patients, 45 in each group.

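### The protocol subdivides placental •NO samples by labour but plans one unadjusted PE-versus-healthy test, and does not say which is the main comparison or how labour enters it

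*Protocol article*

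**What the plan says.** All references are to the protocol article.

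- **Primary study objective.** Placental •NO is one of the measures listed: "Measurement of •NO in placental tissue and O_2_•^−^ in maternal blood using EPR". The case-control arm is to compare the oxidative stress profile between normal and PE pregnancies, and the study hypothesis expects lower placental •NO in PE.
- **Placental concentration of •NO.** Labour is stated to affect the outcome: "Since labour causes ischemia-reperfusion injury at the site of the placenta, which will influence placental NO concentrations". The remedy is that "samples will be subdivided in labour (vaginal delivery, secondary caesarean section) versus no labour (elective caesarean section". No test, combined estimate or interaction is named there.
- **Descriptive statistics and data analysis, matched case-control study.** •NO is in the list of variables compared between PE and healthy pregnancies. If normal, "they will be expressed as mean, standard deviations and 95% confidence intervals and compared using two sided T test"; otherwise they are "compared using Mann Whitney U Test". Labour is not mentioned.
- **Study design, multicentre matched case-control study.** Controls are "matched for maternal and gestational age, parity, smoking behaviour, BMI and ethnic group", with the comment "Matching will reduce the risk of bias". Labour and mode of delivery are not matching factors.
- **Sample size, matched case-control study.** "The sample size of this study will be 90 patients, 45 in each group". This number rests on RHI, not on •NO.

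**The concern.** The laboratory section and the analysis section each fix something about the same primary measure, and they do not refer to each other. A reader cannot tell whether the main •NO result is the pooled comparison, two comparisons by labour, or both.

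Neither route answers the question well.

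- The pooled test leaves out a factor that the protocol itself says changes the outcome and that the matching does not balance. If the share delivered without labour differs between cases and controls, part of any •NO difference is a labour difference.
- Two separate subgroup tests remove that problem, but each uses only part of the 90 women and they may disagree. No overall labour-adjusted answer is described.

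Leaving the choice open also allows it to be made after both results are known.

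**Working it through.** **Inputs from the protocol article.** 45 women per group; two-sided α = 0.05; RHI difference 0.3 and SD 0.5, so a standardised difference of 0.3/0.5 = 0.6.

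**Assumptions, not in the documents.** No-labour share 40% in cases and 10% in controls; labour effect on •NO of 0.5 or 0.8 SD; PE effect on •NO of 0.6 SD, borrowed from RHI because no •NO effect or SD is given.

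**Step 1. The plan's own figure.** n per group = 2(1.96 + 0.842)² × 0.5²/0.3² = 43.6, so 44, as stated. With 45 per group, power at 0.6 SD is 81% (normal approximation) or 80% (noncentral t).

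**Step 2. Pooled test, no PE effect.** L is the labour effect in SD units; p₁ and p₀ are the no-labour shares in cases and controls.

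- Bias = L(p₁ − p₀)
- Variance in each group = 1 + L²p(1 − p)
- Standard error = √[(v₁ + v₀)/45]
- False-positive rate = P(|Z + bias/SE| > 1.96)

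| L | Bias | v₁, v₀ | SE | Bias/SE | False positives |
|---|---|---|---|---|---|
| 0.5 | 0.5 × 0.30 = 0.15 | 1.060, 1.023 | 0.215 | 0.70 | 11% |
| 0.8 | 0.8 × 0.30 = 0.24 | 1.154, 1.058 | 0.222 | 1.08 | 19% |

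If p₁ = p₀ the bias is zero and the rate stays at 5%. The protocol gives no sign for the labour effect, so the direction of any bias is unknown.

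**Step 3. Power by stratum and combined, at 0.6 SD.** Stratum power is from the noncentral t with noncentrality 0.6√[n₁n₀/(n₁ + n₀)]. For the combined estimate the information n₁n₀/(n₁ + n₀) is summed over strata.

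| Stratum (40% vs 10%) | Cases / controls | Information | Power |
|---|---|---|---|
| No labour | 18 / 4 | 3.27 | 18% |
| Labour | 27 / 41 | 16.28 | 66% |
| Combined, labour-adjusted | 45 / 45 | 19.55 | about 75% |

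For the combined line, 0.6√19.55 = 2.65, which gives 76% by normal approximation and 75% with a t distribution on 87 degrees of freedom. (10% of 45 is 4.5, taken as 4.)

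**Step 4. Equal shares.** With 30% no labour in both groups, the strata are 14/14 and 31/31. Separate power is 33% and 64%; combined information is 7.0 + 15.5 = 22.5 and power about 80%. The loss from splitting does not depend on unequal shares.

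**Step 5. Range.** With controls at 5% to 20% and cases at 20% to 60%, power is 11% to 33% without labour and 53% to 75% with labour. The combined estimate has 63% to 81% (normal approximation).

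**The case against.** **The subdivision may only be a classification.** It appears in a laboratory paragraph and does not say that two tests replace the pooled one. It is compatible with a stratified or adjusted model, and a condensed article may leave that model to a fuller document. This stands as a limit: the documents do not say that strata will never be combined. But the analysis section does fix a test for •NO, and that test has no labour term. The point is the unreconciled pair of statements, not missing detail.

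**The bias is hypothetical.** Correct. No delivery or labour rates are given. It is tempting to state that PE women are delivered without labour more often, or that only a handful of controls would fall in the no-labour group, but neither is in the documents. At 5% to 20%, 2 to 9 of 45 controls would be without labour; at 30%, 14 would.

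**Broken pairs.** A reader might infer that the split destroys the matched pairs. The planned tests are already unpaired, so no planned paired analysis is lost.

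**Other placental measures.** A reader might extend the point to eNOS. The protocol links labour only to placental NO, so the documents give no basis for that.

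**Labour arises after PE.** Conditioning on it changes what is estimated, and could itself bias the comparison if disease severity drives both delivery mode and •NO. This stands, but it applies equally to the split that the protocol already makes.

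**The gain is modest.** In the 40% versus 10% example it is about 9 percentage points over the labour stratum alone (75% against 66%). True, but the adjusted model also gives one answer from all the women.

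**Conclusion.** The point holds as an unreconciled analysis of a primary measure. The protocol says labour changes placental •NO, does not match on it, subdivides by it in one section and ignores it in the test fixed in another.

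The size is illustrative. Under the assumed 40% and 10% no-labour shares, the pooled test has about 11% to 19% false positives for a labour effect of 0.5 to 0.8 SD. Separate tests have about 18% and 66% power at the borrowed 0.6 SD, against about 75% for one adjusted estimate. The bias depends wholly on unequal shares and is zero when they are equal. The power cost of splitting remains (33% and 64% against about 80% at 30% in both groups). The change should be made, but the documents do not show that the planned comparison is in fact biased.

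**What to change.** State the same rule in the section on placental •NO and in the case-control analysis section, for example:

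> The main comparison of placental •NO between PE and control pregnancies will use all samples in one model with PE group and labour (yes/no), accounting for the matching by matched set or by the matching variables. The adjusted difference with its 95% confidence interval is the main result. If the data are not normal, the model will be fitted on a transformed scale or a labour-stratified rank test (van Elteren) will be used. Results by labour stratum, the group-by-labour interaction and the unadjusted comparison are supporting.

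One non-normal route should be chosen in advance. The van Elteren test stratified by labour does not use the matching, so the transformed model is closer to the main analysis.

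**Cost.** Wording only: the protocol already classifies samples by labour. The model assumes a common PE effect across labour strata, which the interaction and stratum results let readers judge. Because labour status arises after PE, the estimate should be described as a difference conditional on labour; the supporting unadjusted comparison shows what that conditioning changes.
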